*The NHS Long Term Plan* advises building a ‘digital front door’ connecting health professionals to people^24^ to improve access, coordination, health outcomes and efficiency.^25^ In line with this, ACP records need to be accessible to healthcare professionals across different settings.

Electronic Palliative Care Coordination Systems (EPaCCS) have been specifically designed to facilitate seamless electronic information sharing and enable ACP and end-of-life care decision-making to increase the likelihood of delivering end-of-life care following patient wishes and priorities.^26^,^28^ EPaCCS records are intended for creation by trained healthcare professionals with input from patients and their carers to enable patients to discuss and make decisions about their preferences for end-of-life care such as preferred place of death, the ceiling of treatment and resuscitation status. Once stored, it is expected that information should be shared electronically with different professionals across different settings to inform decision-making, especially in times of crisis (emergency services (NHS 111 and 999), general practice, specialist palliative care services, hospices, etc).^26 27^ Nationally, 175 (83%) clinical commissioning groups (CCGs), now Integrated Care Boards (ICBs), have either implemented EPaCCS or started planning for their implementation.^29^ The Department of Health’s National Commitment for End-of-Life Care has recommended continued EPaCCS roll-out^30^ and they have been endorsed in the ‘Palliative and End-of-Life Care: Statutory Guidance for Integrated Care Boards (ICBs)’.^31^

While EPaCCS offer potential merits, no UK research has yet evidenced (1) to what extent EPaCCS support advance care planning, (2) to what extent EPaCCS have been offered equitably to all those who stand to benefit from them, (3) the effect of EPaCCS on patients’ place of death, and (4) if EPaCCS are associated with the use of health resources at the end of life where care costs are high.^32^

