North West London dataset	CMC records will be linked with the ‘Whole Systems Integrated Care’ (WSIC) dataset. WSIC is an electronic record used by healthcare professionals in North West London, which has a population of 2.4 million, to document essential information about patient care in the region (eight health boroughs, previously defined as CCGs).^65^ The WSIC dataset will include all individuals who have died in North West London within the timeframe spanning from 2010 to 2023. This linkage will allow the creation of two cohorts for comparison: individuals with EPaCCS (CMC) and those without EPaCCS. All decedents with a CMC record within the WSIC catchment area will be identified for inclusion within the linked dataset, while decedents without such records will form the control group. The WSIC dataset includes coded primary, secondary, acute, mental health, community health and social care data. This dataset also includes detailed information on social determinants of health, including ethnicity, and mortality data, including place of death. Cost data is also available as patient-level costs referring to the indicative spend calculated separately for each patient for each healthcare sector. This will be used in a cost minimisation analysis of EPaCCS, and it includes primary care level, acute, community, mental health and social care costs. Data linkage will be carried out by North West London Integrated Care Board and supported by existing data sharing framework.^66^ Figure 1 illustrates the data flow and linkage process. The linked dataset will be de-identified prior to being made available to the research team for the analysis

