Leeds EPaCCS	The Leeds EPaCCS dataset represents a combined dataset from community palliative care providers that includes all primary care practices and two city hospice sites (St Gemma’s Hospice and Wheatfields Hospice) and limited secondary care data (eg, unplanned hospital admissions in the last 90 days of life). This dataset encompasses decedent patient records spanning from 2015 to 2023. It includes linked healthcare records data including primary and secondary care data, such as hospital admissions and diagnosis of severe mental illness or learning disability. The EPaCCS in Leeds covers the entirety of the former Leeds CCG serving a population of around 870 000 people through 94 general practitioners (GP) practices. Since 2019, approximately 50% of all people who die in Leeds have an EPaCCS.^67^ Data for all deaths across Leeds from 2021 to 2023 are also available, including decedents without EPaCCS. This will enable comparative analysis between patients with or without EPaCCS records. The anticipated number of records for inclusion is 15 500 decedent records.
Bradford EPaCCS	The Bradford EPaCCS dataset is collected and shared among healthcare providers (including both NHS and voluntary sector providers) through electronic health records. This dataset includes decedent patient records spanning from 2015 to 2023. This EPaCCS is commissioned across the Bradford and Airedale districts, serving a combined population of 585 000 with approximately 4800 deaths per year. Approximately 48% of all deaths in this area had an EPaCCS record in 2018/19.^68^ The anticipated number of records for inclusion is 17 000 decedent records.

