The study will describe how EPaCCS are used, specifically who creates EPaCCS records and what information they encompass regarding individuals’ preferences for end-of-life care. The study will describe data fields across each of the three datasets and evaluate their completeness. Additionally, a descriptive analysis of the three EPaCCS datasets will be undertaken to describe the creation and content of the records across the three regions. These specific regions were chosen for being large metropolitan areas with varied levels of material deprivation and a high concentration of ethnic minority groups. This analysis will focus on the elements of ACP used to support decision-making at the end of life, which include documentation of the ceiling of treatment, resuscitation status, preferred place of care and preferred place of death. The study will also explore if changes are made to decision-making over time for each of these elements. As the three EPaCCS in the study contain data from different periods in time, we will take into account the different timescales during the analyses. The uptake of EPaCCS will be evaluated by describing the number of records created across different time periods and locations. The study will also investigate the setting of the initial record creation (hospital care, primary care, community care). Furthermore, the study will describe the clinical characteristics of patients such as their diagnosis, performance status, capacity for decision-making, living arrangements and expected prognosis. The study will also describe their socio-demographic characteristics with a particular emphasis on social determinants of health such as age, gender, socioeconomic position and ethnicity. The socioeconomic position will be defined using the Index of Multiple Deprivation (IMD), a standard scoring system based on a range of economic, social and housing data, creating a single deprivation score for each small area of the country. Using methodology previously employed in studies by the research team,^43 44^ an IMD score will be created for each patient based on their postcode which will reflect the deprivation data for the Lower-layer Super Output Area (LSOA) within which the postcode falls. Moreover, the study will investigate across sites the association between social determinants of health and the completion of each of the four previously mentioned ACP elements. Table 2 shows the mapping of the study objectives to data sources and eligibility criteria. Exclusion criteria for all data sources are participants who have chosen National Data Opt-Out and those who have withdrawn consent.

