### Analysis

The data from each of the three distinct EPaCCS will be analysed separately. Individual patient-level EPaCCS data will be accessed and cleaned for each of the three systems. The study will categorise the data into social determinants of health (age, gender, ethnicity, social deprivation), clinical characteristics and elements relating to ACP. The social determinants of health have been identified from existing literature for being associated with poor health experiences and outcomes. The study will assess the completeness of variables in the data, examining patterns of missing data at the individual level and identifying any outlier records. Based on the characteristics of missing data, the study will adopt an appropriate approach to treating missing data for statistical analysis. Several methods will be considered that are appropriate for missing at random and not missing at random data. Though, it is assumed that the missing mechanism will be missing not at random. However, no robust methods of imputing missingness in the independent variables with a missing not at random mechanism have been identified. If imputation was carried out, a sensitivity analysis will be conducted to compare parameter estimates with/without imputation. Missing values for key outcomes will be imputed using gender, age, comorbidity, cause of death, IMD and/or study area.^45^ For each ACP element, documented decisions will be categorised to create an outcome (binary or ordinal) variable for inclusion in logistic regression modelling of the relationship between each of these outcomes, as distinct analyses, and social determinants of health, adjusting for major confounding variables and consideration of random effects/fixed effects (eg, comorbidity). Confounders will be selected using expert knowledge, existing literature, and the completeness and availability of the data. Using the London and Leeds datasets, a dichotomised binary outcome of whether or not a patient has an EPaCCS record will be created for logistic regression, modelling the association between the creation of EPaCCS records and social determinants of health. The study will identify both similarities and differences between the creation, use and content of EPaCCS records in the three EPaCCS cohorts. Mindful of the reported challenges associated with the interoperability of EPaCCS data,^46^ the comparison of datasets will be cautiously approached. We will examine the impact of the significant increase in EPaCCS records in London,^47^ and potentially the two other cities, following the outbreak of COVID-19 in March 2020 in terms of the documentation and completeness of ACP elements within the EPaCCS records. We will carry out a secondary analysis (sensitivity analysis) excluding individuals whose records were created during the COVID-19 pandemic after examining the data and the trend in the creation of EPaCCS records.

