
### Work package 1 outputs

WP1 will provide evidence of the variation in the uptake of EPaCCS across the three regions in the UK and will identify factors associated with unequal EPaCCS access. The study will describe similarities and differences in the content and creation of EPaCCS which will inform the development of standardised EPaCCS in the future. We will work with key stakeholders (EPaCCS providers, ICBs and health professionals) and in close collaboration with local populations to ensure those who promote end-of-life care decision-making facilitated by EPaCCS are more accessible and acceptable to individuals across the social strata. This will also include bespoke training for health professionals in culturally competent and literate care to enable end-of-life care discussions and decision-making.

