### Creating comparative cohorts

This study will take an inclusive approach to defining the cohorts for inclusion in the individual-level analysis, identifying deceased patients who had mention of one of the four main disease-related causes of death in their clinical records within the last year of life (cancer, dementia, heart or lung disease). Based on previous analyses^52^ and publicly available national data,^53^ we hypothesise that 22–30% of the EPaCCS cohort will die in the hospital compared with 45–50% in the non-EPaCCS group. The inverse probability of treatment weighting will be used to account for the confounding resulting from the non-random allocation of EPaCCS to the groups and balance characteristics between cohorts.^54^ First, a multivariable logistic regression will be used to determine the propensity score weights. Factors included in the model to estimate propensity scores will include the confounders selected to be included in the main outcome analysis (such as age, sex, ethnicity, deprivation and primary diagnosis). These confounders will be cautiously selected based on thorough discussions with our team, which includes experts in palliative care, input from the patient and public involvement group with lived experience in end-of-life care, and a comprehensive literature search. Then, for each patient inpatient encounter, a weight defined as the inverse of the probability of the treatment they had received will be calculated. The balance of patients’ characteristics will be assessed visually and by examining the standardised mean differences.^55^

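### Objective 1E models record creation among all decedents, so associations with age, gender, ethnicity and deprivation may mix who was a candidate for a record with who got access to one

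*Protocol article*

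**What the plan says.** The Introduction of the protocol article lists, among the questions not yet answered by UK research, "to what extent EPaCCS have been offered equitably to all those who stand to benefit from them". It also describes advance care planning as a process for adults. The study's recommendations are to concern people with life-limiting illness and their families.

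Objective 1E addresses this question. Under Work package 1, Analysis, "a dichotomised binary outcome of whether or not a patient has an EPaCCS record will be created for logistic regression", with the social determinants as explanatory variables.

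The population is described in three places:

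- Table 1, North West London: "The WSIC dataset will include all individuals who have died in North West London within the timeframe spanning from 2010 to 2023". Decedents with a record are identified, "while decedents without such records will form the control group".
- Table 1, Leeds: "Data for all deaths across Leeds from 2021 to 2023 are also available, including decedents without EPaCCS".
- Table 2, which maps objectives to data sources and eligibility, gives for 1E only deceased patients with or without EPaCCS in these two datasets.

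The text introducing Table 2 adds: "Exclusion criteria for all data sources are participants who have chosen National Data Opt-Out and those who have withdrawn consent". No other exclusion is stated for 1E.

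The section on Work package 1 outputs says that the work package "will identify factors associated with unequal EPaCCS access", and goes on to stakeholder work and staff training.

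A disease restriction (a mention of cancer, dementia, heart or lung disease in the last year of life) appears only in Work package 2, under Creating comparative cohorts, where the text begins "This study will take an inclusive approach to defining the cohorts for inclusion in the individual-level analysis".

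**The concern.** The question is about people who could benefit from a record, but the denominator is everyone who died. Some deaths, for example those from an accident or a sudden event without known illness, would ordinarily not have prompted anyone to create a record. In the 1E outcome they count as record not created, exactly like a person with advanced cancer who was never offered one.

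If the share of such deaths differs by age, gender, ethnicity or deprivation, the groups will differ in the proportion with a record even where candidates in every group are served equally. The model cannot separate the two explanations unless it restricts to candidates or adjusts adequately for the type of death.

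Two uses of the result are at stake. One is the conclusion about unequal access, with the training built on it. The other is Work package 2: the Study design section says that knowing which determinants are associated with record creation will guide how those variables are treated in the later models. The individual-level cohorts there are disease-restricted, so associations from all decedents would be carried into a different population.

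**Working it through.** **Denominator and conclusion compared**

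| Item | Population | Where |
|---|---|---|
| Equity question | People who could benefit | Introduction |
| 1E denominator | All deaths: North West London 2010–2023, Leeds 2021–2023 | Tables 1 and 2 |
| Exclusions | Data opt-out, withdrawn consent | Text introducing Table 2 |
| Conclusion from Work package 1 | Unequal access | Work package 1 outputs |
| Individual-level cohorts in Work package 2 | Four disease groups | Creating comparative cohorts |

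The first and fourth rows concern candidates for a record. The second and third do not limit the data to candidates.

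**Adjustment.** The Study design section says 1E uses multivariable regression. The Analysis section selects confounders by expert knowledge, literature and data availability. Its sentence on 1E names no covariate. Comorbidity is mentioned for the models of ACP elements, and cause of death for imputation. Adjustment for diagnosis or cause of death in 1E is therefore neither fixed nor ruled out.

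**Illustration of size.** The plan gives no figure for 1E to reproduce. Inputs:

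- Overall uptake 0.50. Table 1 gives approximately 50% of all people who die in Leeds since 2019.
- Two groups of equal size (assumed).
- Non-candidate shares *a* and *b* (assumed; the documents give none).
- The same uptake *u* among candidates in both groups, so there is no inequity by construction. Non-candidates have no record (a simplification).

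Formulas: *u* = 0.50 / (1 − (*a* + *b*)/2); *p*₁ = *u*(1 − *a*); *p*₂ = *u*(1 − *b*); crude OR = [*p*₂/(1 − *p*₂)] / [*p*₁/(1 − *p*₁)]. Because *p*₁ + *p*₂ = 1 here, this reduces to OR = [(1 − *b*)/(1 − *a*)]².

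| *a* vs *b* | *u* | *p*₁ vs *p*₂ | Crude OR | Per group for 80% power |
|---|---|---|---|---|
| 5% vs 5% | 0.526 | 50.0% vs 50.0% | 1.00 | – |
| 5% vs 10% | 0.541 | 51.4% vs 48.6% | (0.90/0.95)² = 0.898 | 5,372 |
| 10% vs 20% | 0.588 | 52.9% vs 47.1% | (0.80/0.90)² = 0.790 | 1,133 |
| 10% vs 30% | 0.625 | 56.3% vs 43.8% | (0.70/0.90)² = 0.605 | 250 |

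The last column is for a two-sided 5% test of two proportions. It shows that compositional differences of this kind would reach significance at moderate group sizes. Among candidates only, the OR is 1.00 in every row, by construction.

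The calibration matters little. If 50% is taken as uptake among candidates instead of among all deaths, 10% vs 20% gives 45% vs 40%, OR = (0.40/0.60)/(0.45/0.55) = 0.81. Likewise 10% vs 30% gives 45% vs 35%, OR = (0.35/0.65)/(0.45/0.55) = 0.66.

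**The case against.** The best defence has four parts.

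First, Table 2 uses the same words for 1E and 2A, yet 2A's individual-level cohorts are narrowed later. The table may name only the source, and a full statistical analysis plan is promised. This has some force, but the table also states eligibility. The narrowing for 2A is written out, and nothing narrows 1E. The text as it stands gives an unrestricted denominator.

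Second, 1E is multivariable with covariates still to be chosen. That stands, and it is why the point can only be that the two explanations may mix. The illustrative odds ratios are crude. Differences in composition that run through age, for instance, would be partly removed from the ethnicity and deprivation estimates. But a rule for choosing confounders does not settle who belongs in the denominator.

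Third, a reader might infer that sudden and child deaths could never have had a record, and that differences in cause of death will be reported as inequity. The documents do not support that. They mention neither kind of death and bar no one from having a record. Describing ACP as supporting adults is not an exclusion of children, and a person who dies suddenly may already hold a record for another illness.

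Fourth, all-decedent coverage is a legitimate quantity, and the four-disease definition is an imperfect substitute. It leaves out other life-limiting illnesses, keeps some unexpected deaths, and conditions on having been diagnosed. This stands, and argues for reporting both models.

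**Conclusion.** The concern holds in a limited form. As written, 1E has no age or life-limiting-illness limit and no fixed adjustment for diagnosis or cause of death, while its result is to be read as unequal access among people who could benefit. Its associations may therefore combine differences in candidacy with differences in access.

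How large this is cannot be determined from the documents. Crude odds ratios of 0.90 to 0.60 follow from assumed non-candidate shares of 5% versus 10% up to 10% versus 30%, with equal uptake among candidates and no records among non-candidates. They are not estimates of bias in the planned adjusted model. Age is itself an exposure in 1E, so part of the age association would remain under any eligibility rule.

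The conclusion about who belongs in the denominator does not depend on these figures. It rests on the mismatch between the stated population and the stated reading.

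**What to change.** - Keep the all-decedent 1E model and label it as population coverage.
- Pre-specify beside it a 1E model restricted to adult decedents with a recorded life-limiting illness. Take the diagnosis from sources independent of EPaCCS, because a diagnosis recorded through the register would select on the outcome.
- Start from the four-disease definition under Creating comparative cohorts, and run a broader definition of life-limiting illness as a sensitivity analysis.
- Base any statement about unequal access on the restricted model, and report where the two models differ.
- State whether diagnosis or cause of death is a covariate in each model.

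The cost is mainly analysis-plan wording and one further set of models: the cohort definition and both datasets are already planned for Work package 2. The price is a smaller denominator. Inequity in being diagnosed at all would be visible only in the all-decedent model, which is a further reason to report both.

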### Methods and analysis

### Study design

Objectives 1A–1C will be addressed using descriptive statistics, objectives 1D and 1E using multivariable regression and objectives 2A and 2B using a natural experiment framework, which will allow us ultimately to make conclusions and recommendations about the continued use of EPaCCS.^33 34^ Descriptive statistics and multivariable regression are key tools in quantitative end-of-life research where there is a high reliance on routine data.^35^ However, these methods are not always reliable for generating credible causal estimates of treatment effects.^36^ Provided underlying assumptions are met,^37^ natural experiments can generate causal evidence from observational data, including routinely collected data. These have been little used in end-of-life care research to date,^38^ but may be particularly impactful in a field where randomised trials are infrequent and methodologically challenging,^39^ reliance on routine data is paramount^40^ and selection bias in routine data is a persistent concern.^41^

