### Data sources

The study will use non-identifiable data from three EPaCCS across three distinct geographical locations in the UK, namely London, Leeds and Bradford, which combined have a population of 10.4 million people. These EPaCCS were introduced at different times within the same city and across different cities. This has led to natural variation in exposure, resulting in datasets that cover varying time periods: 2010–2022 in London, and 2015–2023 in Leeds and Bradford. Nonetheless, these EPaCCS are well established and contain a sufficient number of records, as illustrated in table 1, to enable meaningful individual site analyses and answer our research questions. Additional anonymised EPaCCS data from different regions will be considered if made available during the study. The sample size will be determined by the data available in the three datasets and will vary depending on the analysis.

**Table 1 T1:** EPaCCS and data availability

EPaCCS location	EPaCCS specific data
London EPaCCS	Coordinate My Care (CMC) served as the commissioned EPaCCS in London from 2010 to 2022, during which time it was also the largest UK EPaCCS. Covering 32 CCGs serving a population of 8.9 million, this EPaCCS dataset reflects a diverse urban patient population in terms of diagnosis, ethnicity and socioeconomic background. CMC records comprise data from various healthcare settings, including primary and secondary care, hospices and nursing homes. The dataset encompasses demographics, diagnoses, care preferences, the ceiling of treatment, resuscitation status, living circumstances, prognosis, performance status, date and place of death. Additionally, data is available regarding how often the record was accessed by urgent and non-urgent healthcare workers. In later years, patients had the option of starting a ‘MyCMC’ plan, whereby they use a patient portal to input some data themselves. The anticipated numbers for inclusion in the dataset are 140 000 records, of which 100 000 are for deceased patients.

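### Objective 1E names a logistic regression with no allowance for clustering; fitted as written, its deprivation interval would be too narrow by an amount that depends on an unstated practice ICC

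*Protocol article*

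**What the plan says.** The Study design section assigns "objectives 1D and 1E using multivariable regression". The WP1 Analysis section then names the models. For 1D, each ACP element is modelled by logistic regression, "adjusting for major confounding variables and consideration of random effects/fixed effects (eg, comorbidity"); no grouping unit is named, and the only example is a patient characteristic. For 1E, using the London and Leeds data, "a dichotomised binary outcome of whether or not a patient has an EPaCCS record will be created for logistic regression". Nothing is said there about random effects, clustered errors, practice or borough.

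Elsewhere the article describes a grouped structure:

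- **Deprivation** is an IMD score assigned by postcode, and it "will reflect the deprivation data for the Lower-layer Super Output Area (LSOA) within which the postcode falls" (Work package 1).
- **Leeds** is described in Table 1 as "serving a population of around 870 000 people through 94 general practitioners (GP) practices".
- **North West London** comprises eight boroughs (Table 1).
- **Timing:** "These EPaCCS were introduced at different times within the same city and across different cities" (Data sources).

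Table 2 gives objectives 1E and 2A the same two datasets. For 2A, the Individual patient-level analyses section names a mixed effects logistic regression without saying what the random effect is. The Ecological analysis section does name one, the North West London regions. The Reporting guidelines section says a full analysis plan will follow.

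**The concern.** An ordinary logistic regression treats decedents as independent. In 1E, both sides of the model plausibly vary between the same units. Everyone in an LSOA shares one deprivation value, and neighbouring areas feed the same practices. Whether a record exists depends partly on the professionals in the practice and on when the system reached that part of the city. When outcome and exposure are both correlated within practices, the model-based standard error of the deprivation coefficient is too small.

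The 1E result matters beyond its own table. The Work package 1 outputs section relies on it to identify factors behind unequal access, and the Study design section says it will inform how these variables are handled in WP2. An interval that is too narrow would make local differences in record-making look like a more precisely estimated deprivation gradient than the data support.

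**Working it through.** The article states no ICC, standard error or power for 1E, so there is no figure to reproduce. The check is a range calculation for Leeds.

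**Deaths per practice, m.** Two routes:

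- From Table 1: 15 500 records over 9 years (2015–2023), about 50% of decedents with a record, three years of all-death data (2021–2023), 94 practices. 15 500 / 9 = 1722 records a year; 1722 / 0.50 × 3 = 10 333 deaths; 10 333 / 94 ≈ 110.
- Borrowing Bradford's crude death rate from Table 1: 4800 / 585 000 × 870 000 × 3 = 21 415 deaths; 21 415 / 94 ≈ 228.

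The first route assumes records spread evenly over nine years, although the 50% figure applies only since 2019. The second assumes that Leeds has Bradford's death rate. I use both as a range.

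**Variance inflation.** For a covariate partly shared within clusters, deff = 1 + (m − 1) × ρy × ρx. Here ρy is the practice ICC of record creation and ρx the share of IMD variation lying between practices. Both are assumptions. The standard error is understated by √deff, and a nominal 95% interval covers with probability 2Φ(1.96/√deff) − 1.

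Example: m = 110, ρy = 0.05, ρx = 0.3 gives 1 + 109 × 0.05 × 0.3 = 2.63, and √2.63 = 1.62.

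| ρy | m=110, ρx=0.3 | m=110, ρx=0.6 | m=228, ρx=0.3 | m=228, ρx=0.6 | Actual coverage of 95% interval |
|---|---|---|---|---|---|
| 0.001 | 1.02 | 1.03 | 1.03 | 1.07 | 93–95% |
| 0.01 | 1.15 | 1.29 | 1.30 | 1.54 | 80–91% |
| 0.05 | 1.62 | 2.07 | 2.10 | 2.79 | 52–77% |
| 0.10 | 2.07 | 2.75 | 2.79 | 3.82 | 39–66% |

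The first four result columns are the factor by which the standard error is understated.

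**Simulation check.** With 94 practices, no true deprivation effect and 300 datasets per setting, the ordinary logistic interval covered 93–95% with no clustering, 83–92% at ρy = 0.01, 52–78% at 0.05 and 39–66% at 0.10. Practice-clustered standard errors gave 91–96% throughout.

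**LSOA clustering alone.** Assume 1500 residents per LSOA: 870 000 / 1500 = 580 LSOAs, or 18–37 deaths each. IMD is constant within an LSOA, so ρx = 1 and deff = 1 + (m − 1) × ρy. The standard error is understated 1.04–1.09 fold at an ICC of 0.005 and 1.36–1.67 fold at 0.05. Because LSOAs are smaller units, clustering on them does not pick up correlation across the rest of a practice's patients.

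The number of practices in North West London is not given, so I make no equivalent calculation there.

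**The case against.** The strongest reply is that the article never says single-level. It says logistic regression, promises a full analysis plan, and is a condensed document; grouping units and variance estimators are commonly settled in that plan. The 1E sentence also omits confounder adjustment, although the Study design section makes 1E multivariable, so it is evidently shorthand and may be meant to carry over the random or fixed effects considered for 1D. WP1 is described as exploratory, with no test or significance threshold for 1E.

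Much of this stands. A reader might infer that the plan accepts clustering in WP2 and rejects it in 1E. The article does not support that: the individual-level WP2 model names no grouping unit either, and silence in 1E is not rejection. A reader might also infer that the interval is bound to be far too narrow, or that false inequalities will be declared significant. With no ICC in the documents the first cannot be claimed, and with no significance rule the second is not what the article says.

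What the reply does not remove is that the article chooses a model for 1E and, for the same two datasets, names a mixed effects version elsewhere. The clause in the 1D sentence gives no grouping unit to carry over. Followed as written, 1E takes no account of practice.

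**Conclusion.** The concern holds as a weakness in the stated method, with a size that cannot be fixed from the documents. As written, the 1E deprivation interval would be too narrow if record creation is positively correlated within practices. For Leeds the understatement of the standard error is close to nil at a practice ICC of 0.001, modest at 0.01 and serious at 0.05–0.10. This rests on the assumed ICCs, the assumed 30–60% of IMD variation between practices, and 110–228 deaths per practice. The direction does not depend on the particular values. The size for North West London, and any effect on the ethnicity association, has not been established.

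**What to change.** In the WP1 Analysis section, keep the 1E logistic regression and its population-averaged odds ratios, and add that standard errors will be clustered on GP practice in both Leeds and North West London. Do the same for the IMD term in the 1D models wherever a practice code is held.

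Show a model with borough fixed effects or a practice random intercept as a supplementary analysis only. Either changes the question to deprivation differences within a borough or within a practice, and borough fixed effects would remove between-borough differences that may be part of the unequal access 1E is meant to describe. The supplementary model is still useful in North West London, because practice-clustered errors do not absorb correlation between practices in the same borough, and eight boroughs are too few to cluster on reliably.

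If no practice code can be released, cluster on LSOA and say that this is a partial remedy.

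The cost is wider intervals, one sentence of text, a small change in code, and a pseudonymised practice code in the extract. The article does not say whether the de-identified data carry such a code, so it should be requested before the extracts are fixed.
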